## Abstract

**Background:**

Disordered eating behavior and body dissatisfaction affect a large proportion of the Dutch population and account for severe psychological, physical and social morbidity. Yet, the threshold for seeking professional care is still high. In the Netherlands, only 7.5% of patients with bulimia nervosa and 33% of patients with anorexia nervosa are treated within the mental health care system. Easily accessible and low-threshold interventions, therefore, are needed urgently. The internet has great potential to offer such interventions. The aim of this study is to determine whether a web-based treatment program for patients with eating disorders can improve eating disorder psychopathology among female patients with bulimia nervosa, binge eating disorder and eating disorders not otherwise specified.

**Methods/design:**

This randomized controlled trial will compare the outcomes of an experimental treatment group to a waiting list control group. In the web-based treatment program, participants will communicate personally and asynchronously with their therapists exclusively via the internet. The first part of the program will focus on analyzing eating attitudes and behaviors. In the second part of the program participants will learn how to change their attitudes and behaviors. Participants assigned to the waiting list control group will receive no-reply email messages once every two weeks during the waiting period of 15 weeks, after which they can start the program. The primary outcome measure is an improvement in eating disorder psychopathology as determined by the Eating Disorder Examination Questionnaire. Secondary outcomes include improvements in body image, physical and mental health, body weight, self-esteem, quality of life, and social contacts. In addition, the participants’ motivation for treatment and their acceptability of the program and the therapeutic alliance will be measured. The study will follow the recommendations in the CONSORT statement relating to designing and reporting on RCTs.

**Discussion:**

This study protocol presents the design of a RCT for evaluating the effectiveness of a web-based treatment program using intensive therapeutic support for female patients with bulimia nervosa, binge eating disorder and eating disorders not otherwise specified.

**Trial registration:**

The protocol for this study is registered with the Netherlands Trial Registry NTR2415.

## Background

A significant part of the Dutch population suffers from disordered eating behavior and body dissatisfaction. According to a recent review on the epidemiology of eating disorders, the incidence of anorexia nervosa (AN) in the Netherlands over the past decade has remained stable at around 7 per 100,000 persons per year [1]. For bulimia nervosa (BN) the incidence rate has been estimated at 6.1 per 100,000 persons per year [1]. The latest incidence numbers of AN and BN in the Netherlands are, however, from a national primary care study dated 1995–1999 [1]. In a population-based study in six European countries, including the Netherlands, the lifetime prevalence of AN and BN was estimated to be 0.48% and 0.51%, respectively [2]. For the Netherlands, the lifetime prevalence estimates were somewhat lower compared to the other countries (except for Germany) [2]. In addition to AN and BN, the most common eating disorder diagnosis is the category 'eating disorders not otherwise specified’ (EDNOS), including binge eating disorder (BED) [3,4]. In the six European countries studied, the lifetime prevalence of BED was 1.12% [2].

Eating disorders can have severe psychological, physical and social consequences, and clearly affect the quality of life of the patient [5-7]. Despite all the negative consequences, many patients do not seek or receive mental health care [8-10]. Barriers that prevent patients from seeking help include feelings of shame, fear of stigma, a lack of awareness, denial of the disorder, low motivation for treatment, availability of health services, mistrust in the system, and the high cost [11-15]. According to a review by Smink, van Hoeken & Hoek, only 7.5% of all patients with BN and 33% of all patients with AN are treated within the mental health care system [1]. The threshold for seeking professional care is high. Consequently, there is an urgent need for easily accessible and low-threshold interventions.

The internet with its widespread access and increasing usage, offers a great opportunity to administer appealing and accessible interventions for patients with eating disorders. Internet interventions can offer a high degree of anonymity that may encourage patients who are ashamed of their eating problems to seek help. They can also offer instant and easy access to treatment for patients living in rural and remote locations [16-19]. Newly developed internet interventions have already been applied successfully for various mental health illnesses, including alcohol abuse [20-22], depression [23-25] and anxiety disorders [24,26-28].

Several studies have been conducted into web-based interventions designed to prevent eating disorders [29,30]. However, the number of studies that focus on the treatment of eating disorders through web-based interventions is rather limited. A recently conducted systematic review on internet-based treatment of eating disorders [31] found that such treatments were more effective than waiting lists in reducing eating disorder psychopathology, frequency of binge eating and purging, and in improving quality of life. However, according to the authors, the methodological quality of the studies varied. The internet-based treatments the review investigated differed considerably in the intensity of therapeutic support [31]. Some studies involved self-help or minimal contact interventions, whereas others included weekly contact between participants and their coaches or licensed therapists. Research in the field of depression and anxiety has shown that interventions using (intensive) therapeutic support are more effective than self-help or minimal contact interventions [24,32-34]. For web-based treatments on eating disorders, however, similar research is scarce. According to Aardoom and colleagues, face-to-face contacts and therapeutic support seem to increase study compliance and possibly also treatment compliance, as therapist support appears to play an important role in enhancing participants’ motivation [31]. However, more research is needed on the role of therapeutic support in web-based treatments on eating disorders, with regard to the optimal frequency, amount, type and provider of support.

In the Netherlands, several mental health care institutions provide web-based treatments for patients with eating disorders. As far as we know, only two of these interventions have been studied to date [35-37], and just one of them was conducted among the Dutch population of patients with eating disorders (specifically BN) [37]. This study included a randomized controlled trial (RCT) on an asynchronous web-based treatment program with intensive therapeutic support (25 scheduled clinician feedback moments) among Dutch patients with BN. The RCT showed that the intervention was effective in decreasing disordered eating behavior (measured with the EDE-Q; *d* = 1.5, p <0.001) and body dissatisfaction (measured with the BAT; *d* = 0.7, p <0.001) [37]. Also, the frequency of binge eating and purging reduced from 15 and 14, respectively, at pre-test, to 2 and 0, respectively, at post-test (both p <0.001).

So far, the effects of web-based treatments have not been analyzed for patients with BED and EDNOS in the Netherlands. Given the high prevalence of these eating disorders, it would be interesting to investigate whether a web-based intervention would also be appropriate and effective for these patient groups. Therefore, a web-based intervention with intensive therapeutic support was developed for Dutch patients with all types of eating disorders, including AN, BN, EDNOS and BED [38]. The design and content of the intervention were based on a comparable, successful web-based intervention for problem drinkers [20,39].

In 2010, a pilot study tested the web-based intervention with 165 patients with eating disorders to determine its effectiveness and feasibility [40]. A clinically relevant improvement between baseline and post treatment was found for eating disorder psychopathology (measured with EDE-Q, *d* = 1.17, p < .001) and body dissatisfaction (measured with BAT; *d* = 0.86, p <0.001). Also quality of life (measured with the EuroQol-5D [EQ-5D], *d* = 0.32, p < .001), mental health (measured with the Depression Anxiety Stress Scale [DASS], *d* = 0.56, p < .001), and physical health (measured with the Maudsley Addiction Profile Health Symptom Scale [MAP-HSS] and 15 additional eating disorder-specific complaints, *d* = 0.39, p < .001) clearly improved. All of the effects, with the exception of improvement in quality of life, were sustained at six-weeks and six-months follow-up, and participants’ satisfaction with the treatment program was high. However, the pilot study had a nonrandomized design, so the observed improvements could not be attributed exclusively to the web-based treatment program. Furthermore, 46% of the participants ended the web-based treatment program prematurely and no post treatment and follow-up data were available from these participants. Therefore, it was unknown whether they benefited from participating in the intervention. Accordingly, further research into the efficacy of the web-based treatment program and into the group of those who do not complete the program is needed.

### Study aims

The primary aim of this study is to evaluate whether a Dutch web-based treatment program with intensive therapeutic support can improve eating disorder psychopathology among female patients with BN, BED and EDNOS. The secondary aim is to explore whether the treatment program can also improve body image, physical health, body weight, mental health, self-esteem, quality of life, and social contacts. Additional aims include examining participants’ acceptability of the web-based treatment program, adherence to the program, reasons for non-completion, the long-term treatment effects 3, 6 and 12 months after completing treatment, the influence of motivation on treatment adherence and treatment effectiveness, the therapeutic alliance between the participants (completers as well as non-completers) and their therapists, the predictors of treatment effectiveness and treatment adherence, and the additional value of participating in the online forum on the effect of treatment and adherence to it. In line with the conclusions of the review by Aardoom and colleagues [31], the involvement of other interventions during treatment and follow-up, as well as changes in medication use during treatment, will also be monitored and reported.

## Methods/design

### Study design

The present study is a parallel-arm randomized controlled trial that will compare the outcomes of participants assigned to the experimental treatment group (web-based treatment program) with those assigned to the waiting list control group. Figure 1 presents a flow diagram of the study.

**Figure 1 F1:**
[figure not shown]
Flow diagram of the study.

Baseline data for both groups will be obtained from the baseline questionnaire (Q0). After randomization, the participants in the experimental treatment group will immediately start with the web-based treatment program while the participants assigned to the control group will receive informational and supportive no-reply email messages once every two weeks until they can start with the web-based treatment program 15 weeks later. A waiting period of 15 weeks was chosen, as this was the average period of treatment in our pilot study and we assume this will also be the case in the present study. Before the participants in the control group can begin the web-based treatment program, they will be asked to complete the pre-intervention questionnaire (QP) to determine whether there are any differences between the baseline situation and the situation after the 15-week waiting period.

Each participant in the experimental treatment group will receive the post-test questionnaire (Q1) after completing the web-based treatment program. The post-test questionnaire will measure primary and secondary outcomes and the participant’s acceptability of the web-based treatment program. In cases where participants in the experimental treatment group do not fully complete the web-based treatment program within 18 weeks, they will receive the additional questionnaire (QA) 18 weeks after the start of the intervention. This questionnaire will replace the post-test questionnaire (Q1) as the second assessment, to set the period between the first and second assessments as close as possible in both groups. Assessment QA is identical to the post-test questionnaire (Q1), with the exception of the questions to evaluate the web-based treatment program.

The participants in both groups will receive a follow-up questionnaire three, six, and 12 months after completing the treatment program (assessments Q2, Q3 and Q4, respectively).

Each participant who ends the web-based treatment program prematurely will receive the evaluation questionnaire (QE) instead of the post-test questionnaire (Q1). The evaluation questionnaire measures the participant’s reasons for non-completing and the acceptability of the web-based treatment program. In addition, the primary and secondary outcomes will be measured. Each participant will also receive the follow-up questionnaires (Q2, Q3 and Q4).

As a reward for completing the extensive questionnaires, each participant will receive a €10.00 digital coupon to an online store (http://www.bol.com) for each completed research questionnaire. The baseline questionnaire (Q0) is an exception, as this questionnaire is primarily relevant for the therapist, whereas the other questionnaires are primarily relevant for research purposes. Consequently, each participant can receive a maximum of €50.00 for completing all of the research questionnaires.

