#### Waiting list control group (no-reply e-mail messages)

The participants in the waiting list control group will have to wait for 15 weeks after the randomization before they can start taking part in the web-based intervention. During this period, the participants will receive a no-reply email from the researcher every two weeks to keep them involved in the study. To avoid therapeutic support, the participants in the waiting list control group cannot reply to these messages. The email messages will include information about eating behaviors and body image, psycho education, motivational messages, and references to the informational website and online forum.

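### Controls have their second assessment at a fixed 15 weeks; in the experimental arm treatment course sets it, with no stated week for participants who stop early

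*Protocol article*

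**What the plan says.** All of this is in the protocol article, mainly under Methods/design, Study design (the text with Figure 1).

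- **Control arm.** Participants "will have to wait for 15 weeks after the randomization before they can start taking part in the web-based intervention" (Waiting list control group). Before they start they complete QP, "to determine whether there are any differences between the baseline situation and the situation after the 15-week waiting period". This is one fixed time for everyone.
- **Experimental arm, completers.** Each participant "will receive the post-test questionnaire (Q1) after completing the web-based treatment program". No calendar week is given.
- **Experimental arm, not complete by week 18.** "they will receive the additional questionnaire (QA) 18 weeks after the start of the intervention". QA then stands in for Q1 "as the second assessment, to set the period between the first and second assessments as close as possible in both groups".
- **Experimental arm, early stoppers.** "Each participant who ends the web-based treatment program prematurely will receive the evaluation questionnaire (QE) instead of the post-test questionnaire (Q1"). QE includes the primary and secondary outcomes. Its week is not stated.

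The same section explains that 15 weeks was chosen because it was the average length of treatment in the pilot. The experimental arm starts at once after randomization, so the two clocks have practically the same origin.

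**The concern.** One arm is measured by the calendar and the other by how treatment goes. The stated aim is similar intervals in both arms, but the rule limits only the upper end, and it puts that limit 3 weeks after the control assessment. There is no lower limit.

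Two consequences follow. First, the between-group contrast can mix the effect of the program with elapsed time. Second, and more important, the time of measurement for an early stopper is set by stopping, which happens after randomization, in one arm only, and plausibly in relation to how the participant is doing. An early QE is not a missing value that a mixed model handles under its usual assumptions. It is an observed score from another time. If no score is collected near week 15, the analysis cannot recover one.

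The text is also unclear on which score counts. Someone who stops in week 5 has also not completed the program within 18 weeks, so she meets the conditions for both QE and QA. The article does not say which one is her second assessment.

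**Working it through.** **Inputs from the article.** Control assessment at 15 weeks; QA at 18 weeks; at least 7 contacts in Part 1 and 14 in Part 2, at two a week (Experimental treatment group); at least 60% expected to complete, 46% premature ending in the first study, mean difference 1.0, SD 1.2, and 25, 42 and 252 participants (Sample size and power calculation).

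**The plan's own figures.** A repeated-measures ANOVA (between factors, two measurements, correlation 0.95) gives 24 per arm at f = 0.5/1.2 = 0.417 and 25 at f rounded to 0.40. Then 25/0.60 = 41.7, so 42; 42 × 6 = 252; 252/2 = 126 per arm. The calculation has no term for assessment time, so this point leaves the sample size unchanged.

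**Possible times in the experimental arm.**
- Q1: (7 + 14)/2 = 10.5, so from about week 10.5 to week 18.
- QA: week 18, which is 18 − 15 = 3 weeks after control.
- QE: not stated, possibly in the first weeks.

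**How many it touches.** 0.40 × 126 = 50.4, so up to about 50 non-completers.

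**Mean time if nobody stops early.** Assume completion time is normal with mean 15 and SD 2 to 4 weeks, floored at 10.5 and capped at 18. The mean second assessment is then at 14.7 to 14.9 weeks, with 7% to 23% assessed by QA. The means agree, although only 20% to 38% are assessed within one week of week 15.

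**Mean time with 60% completing** (completers assumed at a mean of 13 to 15 weeks).
- Stoppers measured by QE at an assumed mean of 4 to 10 weeks: 0.6 × 13 + 0.4 × 4 = 9.4, up to 0.6 × 15 + 0.4 × 10 = 13.0 weeks. That is 5.6 to 2.0 weeks earlier than control.
- Stoppers measured by QA: 0.6 × 13 + 0.4 × 18 = 15.0, up to 0.6 × 15 + 0.4 × 18 = 16.2 weeks. That is 0 to 1.2 weeks later.
- With 54% completing and QE: 0.54 × 13 + 0.46 × 4 = 8.9, up to 0.54 × 15 + 0.46 × 10 = 12.7 weeks. That is 6.1 to 2.3 weeks earlier.

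So even the direction of the gap depends on the QE/QA question.

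**Bias from elapsed time alone.** Assume linear natural improvement of s points per 15 weeks. The shift in the experimental mean is s × (T − 15)/15; a negative value understates the program.

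| Scenario | s | Shift (EDE-Q points) |
|---|---|---|
| Arm mean at 11.4 weeks (0.6 × 14 + 0.4 × 7.5) | 0.1 to 0.3 | −0.02 to −0.07 |
| 40% at week 6, the rest at 15: −0.4 × s × 9/15 | 0.3 to 0.5 | −0.07 to −0.12 |
| All at week 18 (an upper limit; it does not fit a 15-week average) | 0.1 to 0.5 | +0.02 to +0.10 |

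The values of s have no source in the article. Against the planned 1.0 point, these shifts are small.

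**The case against.** The strongest reply is that the authors saw the problem and dealt with much of it. The wait matches the pilot's average treatment length, QA caps the interval at 18 weeks, and among participants who stay in treatment the mean times come out nearly equal. That stands. It also stands that the time-only bias is small on any drift assumed here, and that in the early-QE scenarios it works against the program.

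A reader might infer several stronger things that the article does not support:

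- **That the mixed model cannot adjust because all second assessments are coded as one visit.** Statistical analysis does not say how time enters the model. Actual assessment time could be used; that would deal with elapsed time, though not fully with timing that depends on outcome.
- **That early stoppers are known to be measured at drop-out.** This is the natural reading of the QE rule, but no week is given, and Figure 1 is not shown here.
- **That early stoppers certainly have no outcome near week 15.** They also receive Q2 to Q4. If Q2 is timed three months (about 13 weeks) from stopping, someone who stops in weeks 2 to 4 would receive it at about weeks 15 to 17. The article does not say when that clock starts for stoppers, and it does not make Q2 their second assessment.
- **That late QA scores favour the program.** QA goes to people who have not finished, and they may have benefited less.

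Moving the primary endpoint to week 15 for everyone is also open to debate. With a 15-week average, many eventual completers would still be in treatment then.

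None of this settles the position of premature enders, for whom neither the matched wait nor the cap sets a time.

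**Conclusion.** The concern holds in a limited form. Assessment is fixed at 15 weeks in one arm and event-driven in the other, and the rule misses its own aim for premature enders: up to about 50 of 126, if completion is at the planned minimum of 60%. QE has no stated week, and its precedence over QA is not stated.

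Bias from elapsed time alone is probably about 0.02 to 0.12 EDE-Q points. That rests on assumed linear drift and assumed assessment times, and the article does not settle its sign. The weightier issue is that the timing of the primary outcome can depend on outcome-related events in one arm, and that week-15 scores not collected cannot be recovered. The article gives no figures to size that part. It does report, under Background, that the pilot had no post-treatment data from the 46% who stopped, and it asks for research into this group.

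This should be fixed, but it does not invalidate the design. Confidence is medium, because the QE week and the coding of time are not stated.

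**What to change.** 1. Send the outcome battery (QA content) at 15 weeks after randomization to every experimental participant who has stopped early, in addition to QE. State that this score is her second assessment in the intention-to-treat contrast; this also settles the QE/QA precedence.
2. For participants still in treatment, send QA at the control arm's 15 weeks instead of 18. Failing that, add a sensitivity analysis that uses actual assessment time. That analysis is useful in either case, since those who complete before week 15 could still be measured up to about 15 − 10.5 = 4.5 weeks before controls.
3. Keep Q1 and QE for program evaluation, reasons for stopping and end-of-treatment outcomes.

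**Cost.** An amendment and a change to the questionnaire dates. Early stoppers get one extra online questionnaire, at 10 euro each: about 50 × 10 = 500 euro if 40% stop. An early stopper would then complete QE, the week-15 battery, Q2, Q3 and Q4, which is 5 × 10 = 50 euro and equals the maximum already stated under Study design. The estimate may be slightly smaller where participants are still in treatment at week 15. Treatment itself and the sample size are not affected.
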